### 7.2 Research Variables Form (RVF)

The table below details all of the assessments that will be carried out over the course of the study, and at what time point they will be carried out.

| Type of data           | Variable name         | Outcomes/units | Source/Any Instructions |
|------------------------|-----------------------|----------------|-------------------------|
| Eligibility assessment | Eligibility Questions | 6 items        | None                    |
| Baseline assessment    | Demographics          | 25 items       | None                    |
|                        | DASS 21               | 21 items       | Lovibond, 1983          |
|                        | PANAS                 | 20 items       | Watson et al., 1988     |
|                        | GSE                   | 10 items       | Schwarzer &             |

|                    |                     |          |                             |
|--------------------|---------------------|----------|-----------------------------|
|                    |                     |          | Jerusalem, 1995             |
|                    | CWSv2               | 32 items | Quirk et al., 2009          |
|                    | TAS 20              | 20 items | Bagby et al., 1994          |
|                    | EQ-5D               | 6 items  | Taylor et al., 1992         |
|                    | LTS                 | 6 items  | Stevens et al., 2010        |
| 1 month assessment | Demographic changes | 6 items  | None                        |
|                    | DASS 21             | 21 items | Lovibond, 1983              |
|                    | PANAS               | 20 items | Watson et al., 1988         |
|                    | GSE                 | 10 items | Schwarzer & Jerusalem, 1995 |
|                    | CWSv2               | 32 items | Quirk et al., 2009          |
|                    | EQ-5D               | 6 items  | Taylor et al., 1992         |
|                    | LTS                 | 6 items  | Stevens et al., 2010        |
| 3 month assessment | Demographic changes | 6 items  | None                        |
|                    | DASS 21             | 21 items | Lovibond, 1983              |
|                    | PANAS               | 20 items | Watson et al., 1988         |
|                    | GSE                 | 10 items | Schwarzer & Jerusalem, 1995 |
|                    | CWSv2               | 32 items | Quirk et al., 2009          |
|                    | EQ-5D               | 6 items  | Taylor et al., 1992         |
|                    | LTS                 | 6 items  | Stevens et al., 2010        |
| 6 month assessment | Demographic changes | 6 items  | None                        |
|                    | DASS 21             | 21 items | Lovibond, 1983              |
|                    | PANAS               | 20 items | Watson et al., 1988         |
|                    | GSE                 | 10 items | Schwarzer & Jerusalem, 1995 |
|                    | CWSv2               | 32 items | Quirk et al., 2009          |
|                    | EQ-5D               | 6 items  | Taylor et al., 1992         |
|                    | LTS                 | 6 items  | Stevens et al., 2010        |
| Exit interview     | Change Interview    | N/A      | Elliot et al., 2001         |

### 7.3 Sample size & Power calculations

The trial will recruit 60 participants, with the aim of having 12 completers per condition. A completer is defined as a participant who has completed the baseline and 1 month assessment. This figure is based on the recommendations of Julious (2005) that a pilot RCT should have a minimum of 12 participants per group.

### 7.4 Planned data analysis

For the quantitative data, normally distributed variables will be summarised by their means and standard deviations, skewed continuous variables by their medians and interquartile ranges and categorical variables by their frequencies and percentages. For the co-primary outcome, we will estimate the difference in means,

between the three groups, together with 95% confidence intervals. Available cases will be used, following intention to treat principles.

Qualitative data from the Exit Interview will be analysed using thematic analysis (Braun & Clarke, 2006); this method will highlight the key themes across interviews in relation to the research question. These themes will be used to adapt the intervention where necessary before proceeding to a definitive trial.

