## 6.3 *Aims & Objectives*

The overall aim of this study is to determine whether PWD improves the wellbeing of older adult caregivers of people with psychosis. The present pilot trial will determine whether the intervention shows promise (determined by between-group effect sizes), and consequently whether a definitive trial is justified. We will use quantitative methods to explore the following aims:

- a) To report the means and standard deviations separated by group allocation for all study time points
- b) To calculate the group (PWD vs WC vs NWC) x time (baseline vs 1 month/ 3 month/ 6 month) effect sizes and associated 95% confidence intervals for the primary outcome measure
- c) To estimate the study recruitment rates
- d) To estimate the study retention rates

We plan to use qualitative methods (exit interviews, and anonymous feedback forms) to explore the following aims:

- a) The acceptability of the conditions (PWD, WC and NWC)
- b) The subjective experience of the conditions
- c) The subjective experience of the research study
- d) What the next steps for the research programme should be

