### 6.5 Assessment process

| Assessment                   | Carried out by | What the assessment is for                                  | How is the assessment carried out            | At what stage is the assessment carried out |
|------------------------------|----------------|-------------------------------------------------------------|----------------------------------------------|---------------------------------------------|
| Baseline Assessment          | RF or RA       | Measure outcomes before randomisation                       | In person
Online or paper based           | After consent                               |
| 1 month assessment           | P              | Measure outcomes post intervention                          | Via post
Online or paper based            | 4 weeks post randomisation                  |
| 3 month follow up assessment | P              | Measure outcomes at short term follow up time point         | Via post
Online or paper based            | 12 weeks post randomisation                 |
| 6 month follow up assessment | P              | Measure outcomes at long term follow up time point          | Via post
Online or paper based            | 24 weeks post randomisation                 |
| Exit interview               | RF or RA       | Generate qualitative data on participants experience of PWD | In person or via telephone
Audio recorded |                                             |

RF= Research Fellow

RA= Research Assistant  
P= participant

The assessment will take place in either the participants own home or in a convenient NHS building (e.g. GP surgery or mental health building). Where assessments are carried out in the participant's home, the lone working policy will be followed (see section 9 – ethical considerations). The assessments at the 1, 3 and 6 month time points will not require any direct contact with the research team. The participants will be sent the assessment pack in the post with a covering letter. They will be asked to complete the questionnaires and return them in a pre-post envelope. Participants will also have the option to complete all assessments online (except for the exit interview).

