#### 6.6 *Randomisation process & allocation concealment*

At the start of the study, the statistician responsible for randomisation will generate a group allocation sequence that will link participant IDs to either positive written disclosure (PWD), writing control activity (WC) or no writing task (NWC). Block randomisation will be used, and will be carried out by a statistician independent of the research team. The statistician will not have access to any of the personal information of the participants and will randomise using the participant identification numbers. Members of the research team will be blind to the size of the blocks. Randomisation will be carried out using a 1:1:1 ratio. The group allocation will be concealed from participants until after the baseline assessment is completed. The researcher responsible for carrying out the assessments will be blinded to the group allocation.

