### 6.9.1 Co-Primary Outcomes:

The co-primary outcome for this pilot trial will be the Positive and Negative Affect Scale (PANAS) (Watson et al., 1988).

- This measure has two subscales: positive affect, and negative affect
- Each scale is comprised of 20 items
- This measure was chosen because we hypothesise that PWD will increase positive moods and reduce negative ones
- This measure has strong internal consistency (Cronbach's  $\alpha > .84$ )

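### Sections 6.3(b) and 7.4 name different estimates for the PANAS, and neither is the baseline-adjusted difference that the pre-randomisation scores would allow

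*Protocol*

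**What the plan says.** Section 6.9.1 makes the PANAS, with its positive and negative affect subscales, the co-primary outcome: "The co-primary outcome for this pilot trial will be the Positive and Negative Affect Scale (PANAS").

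Two sections say how it will be compared between arms.

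- Section 7.4: "For the co-primary outcome, we will estimate the difference in means", "between the three groups, together with 95% confidence intervals". It names no covariate, change score, model or time point. It adds: "Available cases will be used, following intention to treat principles".
- Section 6.3, quantitative aim (b): "To calculate the group (PWD vs WC vs NWC) x time (baseline vs 1 month/ 3 month/ 6 month) effect sizes", also with 95% confidence intervals.

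The baseline score is available. The table in section 6.5 gives the purpose of the baseline assessment as "Measure outcomes before randomisation", and section 6.6 states: "The group allocation will be concealed from participants until after the baseline assessment is completed". The Research Variables Form in 7.2 lists the PANAS at baseline and at 1, 3 and 6 months. Section 7.3 defines a completer as someone with both the baseline and the 1 month assessment, so every completer should have a baseline score.

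**The concern.** Under the plain reading, a difference in group means compares follow-up scores only, while a group by time effect against baseline compares changes. When the arms differ at baseline by chance, the two give different numbers. An analyst following this protocol could report either and point to a section that supports it, and the choice could be made after the data are seen.

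The quantity matters. Section 6.3 says that between-group effect sizes will show whether the intervention has promise and hence whether a definitive trial is justified. Research questions (e) and (f) in section 4.1 concern scaling up and the sample size of that trial. The PANAS contrast is the only between-group estimate with an interval in 7.4.

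The trial is also small: 60 recruited in a 1:1:1 ratio, with 12 completers per arm as the aim, and section 6.6 describes blocking without naming any stratification. Chance differences in baseline affect are therefore likely, and precision is scarce.

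**Working it through.** **Inputs from the protocol.** 12 completers per arm (7.3); 60 recruited at 1:1:1, so 60/3 = 20 per arm at most (7.3, 6.6); 95% intervals (7.4), taken as two-sided. The protocol states no interval width, SD or correlation, so it has no figure of its own to reproduce here.

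**Assumptions.** Results are in units of the outcome SD, taken as equal at baseline and follow-up and pooled over the three arms. The baseline to follow-up correlation r is not in the documents and is varied from 0 to 0.8. Aim 6.3(b) is read as a difference in change scores, which is one natural reading of it.

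**Formulas, n = 12 per arm.**

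- Plain difference in means: t(0.975; 33) × √(2/n) = 2.0345 × √(2/12) = 2.0345 × 0.408 = 0.831.
- Change score: the same × √(2(1 − r)).
- Baseline-adjusted (ANCOVA): t(0.975; 32) × √[(2/n)(1 − r²)(1 + 1/31)]. The factor 1 + 1/31 is the average cost of estimating the slope. With r = 0 this is 2.0369 × 0.408 × 1.016 = 0.845.

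| r (assumed) | Plain difference | Change score | ANCOVA | ANCOVA against plain |
|---|---|---|---|---|
| 0 | 0.831 | 1.175 | 0.845 | +1.7% |
| 0.2 | 0.831 | 1.051 | 0.828 | −0.3% |
| 0.3 | 0.831 | 0.983 | 0.806 | −3.0% |
| 0.4 | 0.831 | 0.910 | 0.774 | −6.8% |
| 0.5 | 0.831 | 0.831 | 0.732 | −11.9% |
| 0.6 | 0.831 | 0.743 | 0.676 | −18.6% |
| 0.7 | 0.831 | 0.643 | 0.603 | −27.4% |
| 0.8 | 0.831 | 0.525 | 0.507 | −39.0% |

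The change score is wider than the plain difference below r = 0.5 and narrower above it. ANCOVA is the narrowest of the three from r = 0.2 to 0.8. It breaks even with the plain difference at r of about 0.18.

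If all 20 per arm were analysed, the plain half-width would be 0.633, and ANCOVA would give 0.639, 0.554, 0.511 and 0.456 at r = 0, 0.5, 0.6 and 0.7.

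**Chance imbalance, n = 12 per arm.**

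- The standard error of a pairwise baseline difference is √(2/12) = 0.41 SD.
- A given pair differs by more than 0.5 SD with probability of about 0.22. At least one of the three pairs does so with probability of about 0.44 (by simulation; about 0.25 at 20 per arm).
- A baseline difference d shifts the plain follow-up difference by r × d on average. At r = 0.6, a one-standard-error imbalance shifts it by 0.6 × 0.408 = 0.24 SD. The mean absolute shift is 0.24 × √(2/π), or about 0.20 SD.

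**The case against.** Four points can be made for the plan.

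1. A reader of 7.4 alone might infer that the plan ignores baseline. It does not: aim 6.3(b) measures effects against baseline. What stands is that the two sections disagree.
2. Section 7.4 does not call the difference unadjusted, and an adjusted mean difference is still a difference in means. Covariates are often left to an analysis plan, and one may exist. This is fair, and silence on a covariate would not be a finding by itself. But a group by time effect and a difference in means cannot both be the single estimate, so any later plan must depart from one of these sections or reinterpret it.
3. The gain depends on a correlation that nobody has stated. This stands: at r of 0.2 to 0.3 it is 3% or less, so it would be wrong to say flatly that the intervals are too wide. The risk runs the other way too, since the worst case for adjustment is a widening of about 2%.
4. This is an external pilot with no hypothesis test in 7.4, and most of its questions (recruitment, retention, fidelity, safety, acceptability) do not depend on the estimator. The SDs needed for planning are reported under aim 6.3(a) in any case. This limits the consequence but does not remove it, because 6.3 judges promise by between-group effect sizes.

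A reader might also infer that the plain difference is biased. Over randomisation it is unbiased. The issue is precision and exposure to the imbalance that happens to occur in this one sample.

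**Conclusion.** The point holds as a conflict between 6.3(b) and 7.4, together with a missed and almost free gain in precision. It is not an error of validity, and the documents do not support a claim that the plan as a whole disregards baseline.

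At 12 completers per arm, adjustment would narrow the interval by about 12% at r = 0.5 and 27% at r = 0.7, would change little at r of 0.3 or below, and would widen it by about 2% at r = 0. These figures rest on an assumed r, on equal SDs over time and on an SD pooled over the three arms. The conflict in wording rests on none of them. The change should be made before any outcome data are seen.

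**What to change.** In 7.4, replace the sentence on the co-primary outcome with wording such as: *For each PANAS subscale, the PWD–WC, PWD–NWC and WC–NWC differences, with 95% confidence intervals, will be estimated at each follow-up from a linear model with arm and the baseline value of that subscale.*

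Reword aim 6.3(b) to the same baseline-adjusted difference, so that both sections name one estimate. If a standardised effect size is also wanted, state which SD scales it.

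Keep all three pairs. Section 7.4 already compares all three groups, and section 6.8.3 includes the non-writing arm to separate the act of writing from its content; WC–NWC is the direct contrast for the act of writing.

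Keep the unadjusted means and SDs by arm and time point as description, and report the baseline to follow-up correlation for each subscale, since planning the definitive trial (research question (f)) will need it.

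The cost is a few sentences, one degree of freedom and a negligible widening if the correlation is near zero. No new data, visits or participants are needed.

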### 7.5 *Dummy results tables*

|           | Positive Written Disclosure |    |    |    | Writing Control |    |    |    | No Writing Control |    |    |    |
|-----------|-----------------------------|----|----|----|-----------------|----|----|----|--------------------|----|----|----|
|           | T0                          | T1 | T2 | T3 | T0              | T1 | T2 | T3 | T0                 | T1 | T2 | T3 |
| Measure 1 |                             |    |    |    |                 |    |    |    |                    |    |    |    |
| Measure 2 |                             |    |    |    |                 |    |    |    |                    |    |    |    |
| Measure 3 |                             |    |    |    |                 |    |    |    |                    |    |    |    |
| Measure 4 |                             |    |    |    |                 |    |    |    |                    |    |    |    |
| Measure 5 |                             |    |    |    |                 |    |    |    |                    |    |    |    |
| Measure 6 |                             |    |    |    |                 |    |    |    |                    |    |    |    |

### 7.6 *Data collection, entering, coding and checking process*

A member of the research team will conduct the data collection. The data will be managed by a research fellow (CH). All data collected post-randomisation will be collected by a member of the research team whom is blind to the condition the participant has been allocated to or it will be completed without the aid of a researcher (i.e. complete the assessment via post). If an assessor is unblinded at any point, another member of the team who is still blind will be assigned to collect the data wherever possible. If the assessor is unblinded during the data collection, then they will continue with the assessment. The individual conducting the assessment will then be instructed to note that they have been unblinded and this will be reported in the final write up of the study.

The data will be entered into an SPSS file by a research assistant (TBC). The research assistant will be blind to the participant group allocation when entering the data; in other words, the quantitative data entry will be blinded. CH and an independent research statistician will be responsible for analysing the research data. The other members of the research team will supervise the processing of the data. The quantitative data from participants will be entered into the SPSS file as it is collected.

Quantitative data will be collected using either assessment booklets or Bristol Online Surveys (an online questionnaire programme). The questionnaire booklets will be in paper form and will be completed using the relevant instructions for each of the questionnaires. Bristol Online Surveys will be used to collect the same data as the assessment booklets, but will be done online so that the participants' responses can be

immediately downloaded onto SPSS. The method of data collection will vary depending on what is most convenient for the participant.

All members of the research team that are involved in the collection and management of data will be given the necessary training on how to use and administer the clinical measures used in this study. Training will involve a meeting with a member of the team who is experienced in using the particular clinical measure to discuss the questions and instructions. Next, the individual will be required to observe an experienced member of the team using the clinical measure, and then for them to be supervised using the clinical measure. If after this training process there are still problems in their use of the clinical measure, any of the training steps may be repeated until a member of the research who is experienced in using the measure, is confident in the individual's ability to use the measure.

Once data entry is complete, a 10% random sample of all assessment booklets will be checked against the data entered by a member of the research team whom has not entered any of the data. The two records will be compared to identify any discrepancies.

With regards to the qualitative data, CH and a research assistant (TBC) will be responsible for carrying out 1:1 interviews with participants, and transcribing these. An interview schedule will be used to ensure consistency across the data collection process. At the point of transcription, all identifiable information will be removed. The data will be transcribed into NVivo, and this programme will be used to carry out the qualitative analysis.

### **7.7 *Missing data policy***

Missing data will be reported but not replaced.

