#### 4.1 *Research question*

This is a pilot study that aims to answer a number of feasibility questions that will determine whether a definitive trial is justified, and if so the design of this trial. Specifically this pilot trial aims to answer the following questions:

- a) Are carers of people with psychosis willing to be recruited and randomised?
- b) Are there retention issues? If yes, at what stages did these occur? What were the reasons?
- c) Are follow-up data complete i.e. no more than 33% attrition?
- d) Can the positive written disclosure (PWD) be delivered with sufficient fidelity?
- e) Is there sufficient evidence for scaling up to a definitive randomised controlled trial?
- f) What sample size is needed to power a full scale randomised controlled trial?
- g) Are there any safety issues or adverse events related to the completion of writing tasks?
- h) What did the carers think of the intervention and study design?

The research question for the definitive trial will be: Does positive written disclosure (PWD) improve both the psychological and physical wellbeing of older adult carers of

people with psychosis compared to a writing (WC) and non-writing control (NWC) condition?

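### The co-primary PANAS comparison is an available-case difference in means with no baseline adjustment named; contrasts with the non-writing control can be biased if dropout relates to baseline affect, and a baseline-adjusted repeated-measures model avoids this without replacing any value

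*Protocol*

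**What the plan says.** Section 7.7 of the protocol gives the missing-data policy in one sentence: "Missing data will be reported but not replaced". It does not separate a skipped questionnaire item from a visit that was not completed.

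Section 7.4 states the comparison for the co-primary outcome: "we will estimate the difference in means" between the three groups, with 95% confidence intervals. The analysis set is given as: "Available cases will be used, following intention to treat principles". The section names neither baseline adjustment nor a repeated-measures model.

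Two places show how much loss is allowed for. Section 4.1 asks: "Are follow-up data complete i.e. no more than 33% attrition". Section 7.3 says: "The trial will recruit 60 participants, with the aim of having 12 completers per condition", and adds: "A completer is defined as a participant who has completed the baseline and 1 month assessment".

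PANAS is collected at baseline and at 1, 3 and 6 months (section 7.2). Section 6.3 uses between-group effect sizes to judge whether the intervention shows promise, and so whether a definitive trial is justified.

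**The concern.** An available-case difference in raw means compares those who replied. It is sound if the people lost resemble, in outcome, the people kept, or if the loss distorts both arms equally. The design gives some reason to doubt this for contrasts with the non-writing control (NWC). Two arms have three 20-minute writing tasks to complete and return, while NWC receives an empty pack. Carers who feel worse at the start may be less likely to finish and reply when there is a task attached. The protocol does not predict this, but its analysis would not correct for it.

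At stake is the effect estimate that feeds the decision on a definitive trial. Bias moves that estimate, and the confidence interval does not show it. Most of the information needed to reduce it, each participant's baseline PANAS, is already collected. Calling a comparison of responders intention to treat, without qualification, also suggests more protection than it gives.

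**Working it through.** **1. The plan's own figures.** The protocol states: "Randomisation will be carried out using a 1:1:1 ratio". So 60 / 3 = 20 per arm. The target is 12 completers per arm, or 36 in all. Implied loss by month 1 is 1 − 36/60 = 40%. Check: 12 / (1 − 0.40) = 20 per arm, and 3 × 20 = 60, which reproduces the stated total. With 33% loss, 20 × 0.67 = 13.4 completers per arm remain.

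**2. Bias from dropout, general form.** Assumptions: true difference 0, outcome SD 1, and a latent normal tendency to stay in that has correlation ρ with the outcome. The mean among those observed is ρ × φ(z_d) / (1 − d), where d is the dropout rate and z_d its normal quantile.

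- d = 0.40: 0.386 / 0.60 = 0.644
- d = 0.33: 0.362 / 0.67 = 0.541
- d = 0.20: 0.280 / 0.80 = 0.350

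The raw difference between two arms with the same mechanism is then:

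| Dropout | ρ = 0 | ρ = 0.3 | ρ = 0.5 |
|---|---|---|---|
| 40% v 20% | 0.00 | 0.294 × 0.3 = 0.09 | 0.294 × 0.5 = 0.15 |
| 40% v 33% | 0.00 | 0.103 × 0.3 = 0.03 | 0.103 × 0.5 = 0.05 |
| 40% v 40% | 0.00 | 0.00 | 0.00 |

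Unequal rates alone therefore do nothing. They are not required either: if opposite kinds of people leave two arms, equal 40% loss gives 2 × 0.644 × 0.3 = 0.39 SD, up to 0.64 SD at ρ = 0.5.

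**3. Dropout driven by baseline.** Here ρ = g × r, with g the correlation of staying in with baseline and r that of baseline with outcome. With g = 0.5, r = 0.6 and 40% v 20% loss, the formula gives 0.3 × 0.294 = 0.088. Simulation gave 0.086 for raw means and 0.00 after baseline adjustment.

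**4. A second dropout model.** The writing arms lose 40%, with log-odds of dropout rising by 0.5 to 1 per SD of baseline negative affect; NWC loses 20% at random. The mean baseline of those kept in a writing arm shifts by −0.19 SD (log-odds 0.5) to −0.33 SD (log-odds 1). Multiplying by r gives the raw bias: −0.19 × 0.5 = −0.10 up to −0.33 × 0.7 = −0.23 SD. Simulation gave −0.10 to −0.23 (rounded) for raw means and −0.004 to +0.002 after adjustment. Both writing arms shift equally here, so the expected bias in PWD v WC is 0.

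**5. Change from baseline is not a substitute.** Under step 3, a raw change score has bias (r − 1) × g × 0.294 = −0.4 × 0.5 × 0.294 = −0.06 SD. The bias reverses sign but does not vanish.

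**6. Precision.** At 12 per arm the unadjusted 95% half-width is t(0.975, 22) × √(2/12) = 2.074 × 0.408 = 0.85 SD. Adjustment multiplies it by about √(1 − r²): 0.866 at r = 0.5 gives 0.73 SD, and 0.714 at r = 0.7 gives 0.60 SD.

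**7. Skipped items (secondary).** If section 7.7 were read to bar proration, the share of scores with at least one blank is 1 − (1 − p)^k for k items and skip rate p. At p = 1% this is 10% for 10 items, 18% for 20 and 28% for 32. At p = 2% it is 18%, 33% and 48%. Both 10 and 20 are shown for a PANAS subscale because section 6.9.1 gives 20 items per scale, while section 7.2 gives 20 for the whole PANAS. The 32-item case is CWSv2. The protocol gives no skip rate.

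**The case against.** This is an external pilot. Describing available cases by allocated group, without imputation, is a defensible choice, and learning how many are lost and why is one of its purposes. The interval of about ±0.85 SD is several times the plausible bias. Section 6.3 already plans group-by-time effect sizes relative to baseline, and their model may sit in a statistical analysis plan that is not shown. The protocol also offers online and telephone completion, which should limit loss.

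Much of this stands. Not imputing is not the fault, and the point is modest. What remains is that section 7.4 does state a method for the co-primary outcome, and a better one costs almost nothing. Wide intervals do not excuse avoidable bias, and adjustment makes them narrower. Effect sizes relative to baseline do not settle it either: if computed as raw change scores they remain biased (step 5).

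Four stronger readings are tempting and are not supported:

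- *One blank item voids a scale.* No section says so. The sentence in 7.7 is compatible with instrument scoring rules, which may be set out elsewhere.
- *Dropout that differs by arm biases the estimates.* Only if it is also related to outcome; otherwise the bias is 0.00.
- *Skipped items push the co-primary outcome below 12 per arm.* The protocol cites advice that "a pilot RCT should have a minimum of 12 participants per group", but defines a completer by assessments completed. At 33% loss and an assumed 1% skip rate, 13.4 × 0.99^10 = 12.1 ten-item scores remain. The figure falls to 13.4 × 0.99^20 = 11.0 only if a fully answered baseline subscale is also required, which the planned comparison does not need.
- *The bias equals the effect sought.* The protocol states no target effect.

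**Conclusion.** The point holds as a recommendation to improve the analysis, not as proof that the planned estimates will be biased. With 33% to 40% loss allowed for, a raw available-case difference against NWC can be off by about 0.1 to 0.2 SD if the writing arms lose 40% and NWC 20% and staying in depends on baseline affect. Baseline adjustment brings this to about 0.

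The arm-specific dropout rates, the strength of the link with baseline and the correlations are all assumptions; the protocol gives none of them. The result for PWD v WC is 0 only if both writing arms lose people in the same way. Adjustment removes bias from dropout that depends on what was observed. It does not remove bias from dropout that depends on unobserved current mood.

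The gain in precision, from about 0.85 to 0.60–0.73 SD, does not depend on any dropout mechanism, only on the assumed correlation of 0.5–0.7. The item-level matter is secondary: a clarification of 7.7.

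**What to change.** - **Section 7.4, model.** Estimate between-group differences for each PANAS subscale at 1, 3 and 6 months with a likelihood-based repeated-measures model on all observed visits, adjusted for baseline PANAS. No missing value is replaced, so section 7.7 can stand.
- **Section 7.4, wording.** Describe the analysis as available cases analysed by allocated group, and drop or qualify the intention to treat label.
- **Reporting.** Give missingness by arm and visit, and the baseline characteristics of those lost by arm and visit.
- **Section 7.7.** State that the no-replacement rule refers to missing visits, and that skipped items follow each instrument's scoring rule or a prespecified proration threshold.

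The cost is a few lines of protocol text and a little analysis and scoring code; no new data are needed. The small downside is that proration assumes the answered items represent the skipped ones.
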